#### EEG Measurement

EEG data are acquired using a portable multichannel EEG system with dry electrodes arranged according to the International 10-20 system, allowing for coverage of the frontal, central, parietal, temporal, and occipital regions. This configuration is suitable for assessing large-scale cortical activity associated with executive control, attention, and response inhibition. EEG signals are sampled at a temporal resolution of 500 Hz, allowing for reliable characterization of both oscillatory activity and task-related event-related potentials (ERPs) in accordance with manufacturer specifications. Resting-state EEG is recorded for a total of 4 minutes under counterbalanced eyes-open and eyes-closed conditions segmented into 1-minute blocks to minimize fatigue and habituation effects. Participants are instructed to remain relaxed and awake and avoid goal-directed cognitive activity during recording.

EEG preprocessing includes band-pass filtering using standard frequency ranges for resting-state and task-based analyses, as well as artifact handling procedures comprising visual inspection and removal of segments contaminated due to eye blinks, muscle activity, movement, or electrode instability. Sessions with excessive artifacts are documented and excluded as appropriate to ensure data quality. During the go/no-go task, EEG is recorded concurrently with behavioral performance. Task-related analyses focus on ERPs associated with response inhibition and cognitive control, specifically, components time-locked to stimulus presentation during go and no-go trials. ERP waveforms are derived by averaging across trials after artifact rejection, with component amplitudes and latencies extracted from fronto-central electrode sites commonly implicated in inhibitory control processes. Longitudinal EEG changes are examined at 6-month intervals using mixed-effects modeling, which accommodates repeated measurements, missing data, and interindividual variability. This analytic approach enables the examination of within-subject changes over time while accounting for relevant covariates, thereby providing sensitive indexes of functional neural adaptation associated with the interventions.

### Data Management

Raw data (including any video recordings) will be kept confidential. Only those directly involved in the project (ie, the researchers and data coders) will have access to the data, which will be stored on password-protected computers and data storage facilities. The results of the project may be published and will be available in the Tun Hussein Onn Sunway Library (Malaysia), but every attempt will be made to preserve participants’ anonymity.

### Cost-Benefit Analysis

We will adopt the integrated cost-benefit analysis and social return on investment approach to comprehensively capture the multidimensional benefits of the cognitive stimulation, physical activity, and combined interventions among older adults in Malaysia. This approach also accounts for broader societal gains for caregivers, families, and the community. Costs will be classified into 5 domains, namely, staff training and other labor, intervention supplies and medical services, venue hire for intervention activities, transportation, and participant time, consistent with the literature [48].

### Statistical Methods

The primary analysis will be conducted using a repeated-measure linear mixed-effects model with time (baseline vs postintervention time point) as a within-subject factor and intervention type (cognitive stimulation vs physical activity vs combined vs control) as a between-subject factor. Participants will be included as a random effect to account for repeated measurements. Analyses will follow the intention-to-treat (ITT) principle, with baseline covariates such as age and sex included as fixed effects where appropriate.

Missing data will be handled using both ITT and per-protocol approaches. For participants with minimal missing data (<15%), analyses will primarily follow ITT principles without imputation, as this level of missingness is unlikely to bias the results. If missing data exceed this threshold, appropriate imputation methods, such as multiple imputation, will be applied. Sensitivity analyses will also be conducted to ensure robustness across both ITT and per-protocol analyses.

For exploratory purposes, paired 2-tailed *t* tests may be conducted to compare outcome values (before and after the intervention for each intervention phase, eg, telomere length), and one-way ANOVA may be used for simple between-group comparisons at a single time point. Results with a *P* value of less than .05 will be considered statistically significant, with appropriate attention to multiple testing for secondary analyses.

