### Sample Size

Simulation-based power analysis was performed using the *superpower* R package [46] in RStudio (version 2023.06.1; Posit PBC). This analysis determined that a sample size of 80 participants per intervention group would be sufficient to detect a medium effect size (η^2^_p_=0.06) in a 2 × 2 mixed-design interaction with 86.6% power. The 2 × 2 design was chosen as a comparison of pre- and postintervention measures between an intervention and control group, providing a basic assessment of whether a specific intervention is effective. This assumes a correlation of at least 0.8 between repeated measures. We calculated that a sample of 400 would be necessary to reach our goals, given that we expect an attrition rate of 20% (80/400 participants) between the pre- and postintervention phases for several reasons (ie, death, decline in health, and dropouts in training sessions).

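### The primary model compares change scores instead of adjusting for baseline, which gives up at most 10% of variance at the plan's own correlation: an optional efficiency gain, not an error

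*Protocol article*

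**What the plan says.** Statistical Methods in the protocol article gives the primary analysis as a "repeated-measure linear mixed-effects model with time (baseline vs postintervention time point) as a within-subject factor". Group enters this model with four levels and no stated restriction on the baseline means. To handle the repeated values, the section adds: "Participants will be included as a random effect to account for repeated measurements". On covariates it says only "with baseline covariates such as age and sex included as fixed effects where appropriate". It names neither the baseline value of the outcome as a covariate nor a constraint that the four groups share one baseline mean.

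The Sample Size section is built on the same kind of contrast. It states that "a sample size of 80 participants per intervention group would be sufficient to detect a medium effect size" (partial eta squared 0.06) "in a 2 × 2 mixed-design interaction with 86.6% power", and then: "This assumes a correlation of at least 0.8 between repeated measures".

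Trial Design describes quasi-random allocation by experimenters in a sequential cycle, without blinding. Logistical adjustments are anticipated for fewer than 15% of the intervention sample.

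**The concern.** When baseline is a level of the time factor and each group has its own baseline mean, the group-by-time contrast with two complete time points is the difference in mean change between groups. A change score subtracts the whole baseline value (slope 1). The best linear predictor of follow-up, with equal variances, subtracts only r times that value. The surplus adds noise whenever r is below 1.

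Age and sex do not recover this loss, because as main effects they leave a within-person contrast unchanged. The covariate list is open, but the same baseline value cannot sensibly be both an outcome row and a covariate in one model.

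What is at stake is precision. Enrolment is closed at 400, so the choice of analysis is one of the few ways left to gain it. A single correlation of at least 0.8 is assumed for primary outcomes as different as the MoCA, behavioural tasks, EEG measures and salivary markers, and the intervention runs for 4 years. Change scores lose power faster than adjusted comparisons when the correlation is lower.

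**Working it through.** **Inputs.** n = 80 per group, partial eta squared 0.06, r at least 0.8, stated power 86.6% (Sample Size); significance level 0.05 (Statistical Methods). Assumptions made here: equal SD at both times, a random intercept, and complete data unless stated.

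**Stated power.** f² = 0.06/0.94 = 0.0638. Noncentral F with df 1 and 158, λ = 0.0638 × 158 = 10.09, gives 88.4%. That is within 2 points of the simulated 86.6%, so the stated figure is reproduced. Working back, 86.6% needs λ = 9.526. With λ = nD²/[4(1 − r)] at r = 0.8, this is a difference in mean change of D = 0.309 SD.

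**Variances of the group contrast (in SD²).**
- Change score: 4(1 − r)/n. At r = 0.8: 0.8/80 = 0.0100.
- Baseline-adjusted: 2(1 − r²)/n. At r = 0.8: 0.72/80 = 0.0090.
- Ratio, adjusted to change: (1 + r)/2 = 0.90. Loss: (1 − r)/2 = 10.0%.
- Standard error: 1 − √0.90 = 5.1%.
- Sample size for equal precision: 80 × 0.90 = 72 per group.

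**Power for the same D = 0.309 SD** (df 158 for change, 157 for adjusted):

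| r | variance given up | change score | baseline-adjusted |
|---|---|---|---|
| 0.90 | 5.0% | 99.1% | 99.4% |
| 0.85 | 7.5% | 94.3% | 95.8% |
| 0.80 (plan's minimum) | 10.0% | 86.6% | 89.9% |
| 0.70 (assumed) | 15.0% | 70.7% | 77.5% |
| 0.50 (assumed) | 25.0% | 49.2% | 61.0% |

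The last two rows lie below the plan's stated assumption and show sensitivity only.

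**Two refinements at r = 0.8.**
- A simulation of 20,000 trials with 80 per group gave a variance ratio of 0.908, a loss of 9.2%. It is slightly under 10% because the adjustment slope has to be estimated.
- If the mixed model keeps the baselines of dropouts (100 per group at baseline, 80 at follow-up), the per-group variance is 0.36/80 + 0.04/100 = 0.0049, against 0.36/80 = 0.0045 for the adjusted analysis. The loss is 0.0004/0.0049 = 8.2%.

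**The case against.** The strongest reply is that nothing here is inconsistent. The power calculation and the primary model use the same kind of contrast, and the estimator is valid. That stands. A reader might infer that the stated power is wrong or the trial underpowered because of this model. The documents do not support that, since 86.6% was computed for this unadjusted interaction.

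A reader might also infer that at least 10% of precision is lost. The bound runs the other way: the plan's 0.8 is a minimum and the loss shrinks as r rises.

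The second reply is that free baselines are defensible here. Allocation is an unblinded sequential cycle, and some participants are placed for logistical reasons such as access to internet-enabled devices, which could be related to baseline cognition or socioeconomic status. It is tempting to answer that intention-to-treat keeps everyone in the arm given by the cycle, but the article does not say so; the moves may be part of the assignment itself. This objection weakens the equal-baseline premise without removing it, because the moves are expected in fewer than 15% of the intervention sample.

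It would also be wrong to say that change scores ignore chance imbalance. They correct it with slope 1, which over-corrects when r is below 1.

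A third reply is that such detail belongs in an analysis plan that is not shown. A common-baseline constraint could indeed be added there without contradicting the article. But the article states its primary model, and as written that model has neither the constraint nor the baseline adjustment.

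Last, the Results section says that analyses of intervention outcomes are under way, so a late switch could look data-driven. That stands and governs the timing of the fix.

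**Conclusion.** The point holds as a missed efficiency gain. Under the plan's own assumption the primary model gives up at most 10% of variance, about 5% of the standard error. That is about 3 power points at r = 0.8 and less above it. The loss exceeds 10% only for an outcome whose real 4-year correlation is below 0.8, and the article gives no data by which to judge that for any outcome. The figures rest on equal SDs over time, a random intercept and baselines that are comparable in expectation. Neither the stated power nor the validity of the planned contrast is in question, so this is an optional improvement.

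**What to change.** Before comparative outcome results are examined:

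- Specify the primary analysis as follow-up values on group with the baseline value of the same outcome as covariate, or as the same mixed model with one common baseline mean for all four groups.
- State that participants are analysed in the arm originally given by the sequential cycle.
- Keep the planned free-baseline model as a sensitivity analysis, because of the logistical moves.

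The cost is wording only, since baseline values are already collected. There are two downsides. The gain relies on comparable baselines, which unblinded sequential allocation with moves supports less firmly than true randomisation; a marked difference between the two models would be a warning. The change must also be dated and documented as made before results were seen.

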**Objective:**

We aim to examine whether our long-term intervention packages can, over 4 years, significantly slow down the normal rate of aging-related decline in cognitive function and brain structure and function, as well as assess changes in aging-related salivary biomarkers. We will also measure the economic impact of such interventions in a cost-benefit analysis.

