### Main Objectives

The main objectives of this study are to (1) examine whether these interventions can, over 4 years, significantly slow down the normal rate of aging-related decline in cognitive function, physical performance, and brain activity and measure the economic impact of such interventions; (2) test hypotheses derived from aging-related theories; (3) provide robust, measurable evidence in both the short and long term and validate meaningful interventions (positive results or improvements in cognition, mental, and physical health that we are going to implement as being acceptable and sustainable in the long term); and (4) provide a quantifiable cost-benefit ratio for suggested solutions.

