## Methods

### Trial Design

This quasi-randomized controlled trial has a longitudinal mixed-subject design for a total of 4 years (between-subject: intervention type; within-subject: repeated measures on various tasks and assessments). Participants will be quasi-randomly allocated to 1 of the 4 groups (cognitive stimulation, physical activity, combined cognitive stimulation and physical activity, and control) in a sequential cycle by experimenters to ensure balance in group sizes. Minor adjustments may be made for a small proportion of participants (anticipated to be fewer than 15% of the intervention sample) to accommodate logistical feasibility, such as availability during intervention sessions or access to required resources (eg, internet-enabled devices for online cognitive sessions). These adjustments will be applied only when necessary. Participants and experimenters will not be blinded to group assignment. Participants will be tested at baseline and every 6 months until the end of 4 years. Structural magnetic resonance imaging (MRI) will only be performed at baseline and at the end of the intervention period.

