#### Interim Measurements

Throughout the intervention period, participation in intervention components will be assessed via both self-reports and interviewer-administered surveys. The MoCA, cognitive behavioral measurements, EEG, and saliva collection will be repeated every 6 months.

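### For outcomes measured every 6 months, the primary model uses baseline and one unspecified later point, so 7 of 9 visits play no part in the primary test of a question about rate of decline

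*Protocol article*

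**What the plan says.** Under Statistical Methods, the protocol article names a linear mixed model as the primary analysis. It has four arms between subjects, participant as a random effect, and "time (baseline vs postintervention time point) as a within-subject factor". Which visit counts as the later point is not stated. The Sample Size section has the same structure: a 2 × 2 pre/post comparison of one intervention arm with control, 80 per arm, partial eta squared 0.06, correlation of at least 0.8, power 86.6%, and 20% attrition from 400.

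The data collected are much richer. Trial Design says "Participants will be tested at baseline and every 6 months until the end of 4 years", and Interim Measurements says "The MoCA, cognitive behavioral measurements, EEG, and saliva collection will be repeated every 6 months". Structural MRI is the stated exception: it "will only be performed at baseline and at the end of the intervention period". Everyday problem-solving and the Iowa gambling task are listed at baseline but not among the 6-monthly measures.

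The Objective in the abstract is to "significantly slow down the normal rate of aging-related decline in cognitive function and brain structure and function", and Main Objectives repeats the aim. For EEG, a primary outcome in the Results section, the EEG Measurement section says "Longitudinal EEG changes are examined at 6-month intervals using mixed-effects modeling".

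For exploratory purposes, paired "tests may be conducted to compare outcome values (before and after the intervention for each intervention phase, eg, telomere length"), and one-way ANOVA may compare groups at a single time point. Missing data below 15% are left without imputation; above that, methods such as multiple imputation apply.

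**The concern.** A question about rate of decline, with 9 measurements per participant, is tested with two of them. Three things follow.

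- The primary test may be less precise than the data allow, and it says nothing about when arms separate.
- A participant who leaves at, say, month 30 has given several post-baseline scores that the primary model never sees. The Sample Size section names declining health as one reason for leaving, so those scores are informative about the missing endpoint.
- EEG has two different models in two sections, and nothing says which is primary. MoCA, the cognitive tasks and saliva share the EEG schedule but are given only the two-level model.

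The later point is also not tied to month 48. Outcome papers are expected from 2026, whereas 4 years from a 2023 start ends in 2027. The only tests tied to individual 6-month phases are before/after tests with no control comparison.

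**Working it through.** **Inputs.** From Sample Size: 80 per arm, partial eta squared 0.06, r = 0.8, 20% attrition (100 enrolled per arm, 80 completing). From Trial Design: visits every 6 months for 4 years. From Statistical Methods: alpha 0.05. Assumed, because the article does not give it: the covariance over the interim visits.

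**1. Visits.** 48/6 + 1 = 9 time points. A two-level factor uses 2 and leaves out 9 − 2 = 7. For MRI it leaves out none.

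**2. The plan's own power.** f² = 0.06/0.94 = 0.0638. Noncentrality = 0.0638 × 158 = 10.09. Noncentral F(1, 158) at alpha 0.05 gives 88.4%. The stated 86.6% comes from simulation and is within 2 points. Attrition also agrees: 400 × 0.8/4 = 80.

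**3. Slope on 9 visits against two points, no dropout.** In units of baseline variance, the two-point variance of change is 2(1 − 0.8) = 0.40. Split this into residual variance s² and variance of true 4-year change v, with 2s² + v = 0.40. For 9 equally spaced visits, the variance of the fitted 4-year change is v + s² × 64/60. Power uses noncentrality 10.09 × 0.40/variance.

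| Structure | s² | v | Variance, 9 visits | Ratio to 0.40 | Power |
|---|---|---|---|---|---|
| Compound symmetry | 0.20 | 0 | 0.213 | 0.53 | 99.1% |
| Random slope, 25% of change variance | 0.15 | 0.10 | 0.260 | 0.65 | 97.5% |
| Random slope, 50% | 0.10 | 0.20 | 0.307 | 0.77 | 95.0% |
| Random slope, 75% | 0.05 | 0.30 | 0.353 | 0.88 | 91.9% |
| AR(1), r = 0.8 at 48 months (generalised least squares) | – | – | 0.400 | 1.00 | 88.4% |

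**4. What baseline-only participants add to the two-point model.** With 80 complete and 20 baseline-only per arm, the likelihood estimate of an arm's change has variance (1 − r²)/80 + (1 − r)²/100 = 0.36/80 + 0.04/100 = 0.0049. Completers alone give 0.40/80 = 0.0050. The gain is 2%.

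**5. Month-48 contrast using all visits.** Visit is categorical, variance at both ends is 1, r = 0.8, and 20 dropouts per arm are spread evenly (2.5 after each of the first eight visits). Per-arm variance of change, against 0.0049 for two points:

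- compound symmetry: 0.00464 (5% lower)
- random slope 25/50/75%: 0.00461/0.00455/0.00445 (6/7/9% lower)
- AR(1): 0.00451 (8% lower)

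With complete data this contrast has the same variance as the two-point one. The larger gains in step 3 belong to the slope.

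**6. Exploratory paired t test.** Suppose a shift of 0.2 SD from practice or ageing, with no intervention effect. The SD of change is √0.40 = 0.632, and the noncentrality is 0.2/0.632 × √80 = 2.83. P < .05 then occurs 79.8% of the time.

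**The case against.** The strongest defence is that the two-point contrast is sound. Arm by time from baseline to year 4 is a controlled comparison of average change, it answers the mean-rate question, and it is exactly what the sample size was built for. That stands.

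Several stronger readings are tempting, and the article does not support them:

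- **That dropouts contribute nothing, making this a completer analysis.** In a likelihood-fitted mixed model, baseline-only participants enter through the pre/post correlation. The precision gain is only 2%, but the handling of bias differs. In a simulation with no true change and dropout depending on baseline, completers showed −0.034 SD and the likelihood estimate 0.001. Multiple imputation is also foreseen above 15% missingness and could draw on interim visits, although the threshold is worded per participant. What remains is that the primary model itself does not use dropouts' interim scores.
- **That more visits must raise power.** Under AR(1) the slope gains nothing.
- **That phase effects rest on uncontrolled t tests.** Those tests are exploratory and optional, and a between-group ANOVA is allowed beside them. It ignores baseline, however, so it only partly fills the gap.
- **That interim data are thrown away.** They are absent from the primary model only; EEG has its own longitudinal model, and the article does not say that other interim data go unused.

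**Conclusion.** The point holds as a question of efficiency and consistency, not of validity. For MoCA, the cognitive tasks and saliva, 7 of 9 visits play no part in the primary test. For EEG, two sections specify different models. The article fixes the two-level factor explicitly and repeats the pre/post design in its power calculation, so this is more than detail left to a fuller document.

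The cost ranges from none (AR(1)) to about 47% of the variance (compound symmetry) for a slope without dropout, taking power from about 88% to between 88% and 99%. For a month-48 contrast with 20% evenly spread dropout it is about 5 to 9%. Both ranges rest on r = 0.8 over 4 years and on assumed covariance structures. Loss of the trajectory and of dropouts' interim scores from the primary model does not depend on those assumptions.

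**What to change.** For the outcomes measured every 6 months, make the primary analysis a mixed model on all visits. Treat visit as categorical with unstructured covariance, or use a random intercept and slope. Name the arm-by-visit contrast at month 48 as the primary test and the arm-by-time slope as supportive. State that this also governs EEG, so that the two sections agree.

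Do not carry a participant intercept alone over to 9 visits. With s² = 0.10 and v = 0.20, simulation of that model gave type I error of about 20%, against 5.1% with random slopes. This is a warning about the extension, not a fault of the two-point model now written.

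Keep the two-point model for outcomes without 6-monthly measurement: MRI and, as scheduled, everyday problem-solving and Iowa gambling. Define their later point. Replace the exploratory paired t tests and single-time ANOVAs with arm-versus-control phase contrasts from the all-visit model.

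The cost is a change of wording with no new data. The downside is a slightly more complex model with a covariance assumption, plus linearity for the supportive slope, which the categorical fit allows one to check.

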#### Intervention Group 2: Physical Activity

The physical activity intervention will comprise walking, dancing (Zumba), resistance training, and qigong sessions. These physical activity interventions are age appropriate and ecologically sound, with the potential to be adopted as part of participants’ healthy aging practices. For 6 months, participants will attend a weekly hour-long session of one of the aforementioned activities. Every 6 months, the participants in the physical activity group will alternate among the 4 above-mentioned physical activities until the end of the 4-year intervention period.

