#### Record of Attendance

Attendance to each intervention session will be recorded, and participants will be asked to submit a weekly Google Form to record details of activities they have done over the previous week in their free time, which include physical, cognitive, social, and leisure activities not part of the intervention. This will be helpful for us to observe and control the frequency of other nonintervention activities while participants take part in the intervention.

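### The primary model and sample size treat participants as independent in every arm; if active-arm sessions are shared classes, standard errors for active-arm contrasts will be too small

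*Protocol article*

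**What the plan says.** Statistical Methods sets out a linear mixed model with time within subjects and "intervention type (cognitive stimulation vs physical activity vs combined vs control) as a between-subject factor". Its random part is given in one sentence: "Participants will be included as a random effect to account for repeated measurements". The test level is a P "value of less than .05 will be considered statistically significant".

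Sample Size states that "a sample size of 80 participants per intervention group would be sufficient" for a pre/post comparison of one intervention with control (partial eta squared 0.06, repeated-measures correlation 0.8, power 86.6%). It then allows for 20% attrition to reach 400. It has no term for correlation between participants.

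On delivery, the single-modality arms have one session of an hour each week and the combined arm has two; activities change every 6 months. In the physical arm, "The physical activity intervention will comprise walking, dancing (Zumba), resistance training, and qigong sessions". Study Setting places physical activity on one campus, apart from two kinds of walk, and cognitive stimulation online. Trial Design lets allocation be adjusted for reasons "such as availability during intervention sessions". Under Record of Attendance, "Attendance to each intervention session will be recorded". Controls attend no intervention sessions.

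**The concern.** People taught together share a leader, peers and a time slot, so their changes over time may be alike. A model whose random part is the participant handles correlation between one person's visits but treats different people as independent. If classes matter, the active arms hold less information than the model assumes, and a good or poor class or leader is partly read as an effect of the modality. Controls attend no sessions, so the correlation would arise on the active side only; this is a partially nested design.

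At stake are the tests of each intervention against control. Also at stake is the prediction in the Introduction that the combined arm will do best, because both sides of that comparison may be clustered.

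**Working it through.** **1. The plan's own figures.** With 80 per group, f² = 0.06/0.94 = 0.0638. A noncentral F(1,158) with λ = 0.0638 × 158 = 10.1 gives power 88.4%, within two points of the simulated 86.6%. Enrolment: 4 × 80 = 320, and 320/(1 − 0.20) = 400. Both reproduce, with participants independent.

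Solving for exactly 86.6% gives λ = 9.526, a standardised difference in change of d = √(9.526 × 2/80) = 0.488. This is used below.

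**2. Are sessions shared?** The article does not say so; this is inference. 400/4 = 100 people per arm. One-to-one delivery would need 100 + 100 + (2 × 100) = 400 session-hours every week for 4 years. Together with set session times, attendance records, a single campus, and Zumba and qigong as activities, this makes shared sessions very likely for physical activity. Online gaming and puzzles could be done individually.

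**3. Formulas.** Let m be class size and ICC the within-class correlation of change. Both are assumptions: m = 10 to 25, ICC = 0.01 to 0.05.

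- Design effect in an active arm: DEFF = 1 + (m − 1) × ICC
- True to assumed standard error against unclustered control: √((1 + DEFF)/2)
- Same ratio between two active arms with separate classes: √DEFF
- True type I error: 2 × P(Z > 1.96/ratio)
- Power against control once clustering is allowed for: Φ(0.488/√((1 + DEFF)/80) − 1.96)

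**4. Results.**

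| m | ICC | DEFF | SE ratio vs control | Type I vs control | Power vs control | SE ratio, active vs active | Type I, active vs active |
|---|---|---|---|---|---|---|---|
| any | 0 | 1.00 | 1.00 | 5.0% | 87.0% | 1.00 | 5.0% |
| 10 | 0.01 | 1.09 | 1.02 | 5.5% | 85.5% | 1.04 | 6.0% |
| 20 | 0.05 | 1.95 | 1.21 | 10.7% | 72.0% | 1.40 | 16.0% |
| 25 | 0.05 | 2.20 | 1.26 | 12.1% | 68.4% | 1.48 | 18.6% |

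For m = 20 and ICC 0.05: DEFF = 1 + 19 × 0.05 = 1.95; √(2.95/2) = 1.214; 1.96/1.214 = 1.614, so the error is 10.7%. A simulation of 20,000 trials with clustering ignored gave 10.5%. The normal approximation returns 87.0% rather than 86.6% with no clustering, so the power column is very slightly generous at baseline. It also takes no account of the few classes available: 80/20 = 4 per arm.

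**5. What the table assumes.** Each person stays in one class throughout. The last two columns also assume that no class contains people from two arms. The article settles neither.

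**The case against.** The strongest reply is that the premise is inferred. No section says sessions are held in groups, who leads them or how many classes there are. The Cost-Benefit Analysis section lists staff labour and venue hire as cost domains, which does not describe delivery. This stands, so the point has to be conditional. A reader might infer that the intervals are certainly too narrow in every active arm; the article does not support that, least of all for the online cognitive arm.

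Nor is there support for reading the same classes as lasting all 4 years. Activities rotate every 6 months, and nothing says that classes or leaders carry over. Re-forming them would dilute the correlation.

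A reader might also conclude that active-versus-active contrasts are necessarily worse affected. That needs separate classes. If combined-arm participants sit in the same sessions as the single-modality arms, part of the class effect cancels and the inflation is less.

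It can also be said that a condensed article leaves random-effects structure to the analysis plan, and that naming one random effect does not exclude others. This has some force. But the article does specify the random part of its primary model and gives its purpose, and its power calculation also assumes independence. If a fuller plan has a class term, the article's description needs to be brought into line.

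**Conclusion.** The point holds in conditional form. As described, neither the model nor the sample size can detect or absorb correlation within classes, and the likely mode of delivery makes such correlation plausible in the active arms only.

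The size rests on assumed class sizes and ICC. Over the assumed range the effect against control runs from practically negligible to more than double the nominal error. The lower part of that range would change little; the upper part would also take power well below the stated 86.6%. The active-versus-active figures apply only to separate classes. The change is worth making because the class information is needed to tell these cases apart, the intervention is still running, and outcome papers are expected from 2026.

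**What to change.** - **Session format.** State whether each activity is delivered in shared sessions, with the number of classes, their sizes and leaders, and whether combined-arm participants join the single-modality sessions.
- **Attendance record.** Add class and leader identifiers for each 6-month phase, and recover past phases from existing logs where possible.
- **Statistical Methods.** Add class-by-time random effects for the active arms only, with each control as its own cluster. Use separate, crossed effects for cognitive class and physical class, since a combined-arm participant belongs to one of each. Use small-sample degrees of freedom.
- **Definition of class.** Use the class assigned or scheduled, not the class attended. Attendance arises after allocation and is undefined for people who never come, who must stay in the intention-to-treat analysis. Fit multiple membership across phases as a sensitivity analysis.
- **Single class or leader.** Where an activity has only one, state that its effect cannot be separated from that of the modality.
- **Sample Size.** Restate the 86.6% power over a range of ICC.

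The cost is a few log fields, some work to reconstruct earlier phases, and analysis wording. Confidence intervals will be somewhat wider, and the class variance will be estimated from few classes and so imprecisely.
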